### Ethics

The trial is approved by the local ethics committee (EC) of Shanghai Pulmonary Hospital (L20-385-1). The whole procedures for trial implementation, evaluation, and filing stated in this plan are designed to ensure that researchers follow the guidelines of the ‘Clinical Trial Management Practice’ and the ‘Declaration of Helsinki’. The investigator can change the plan to eliminate the possible risks that the patient may face without the EC approval. Explains and amendments should be immediately submitted to the EC. Written informed consent should be obtained from all participants after a full explanation of this study (Trial registration number: ChiCTR2000032403).

### Sample size

Previously, BPA shows to result in reducing pulmonary vascular resistance from 7.3±3.2 WU to 3.8±1.0 WU (mean ± SD) within 6 months [15], while riociguat is reported to decrease pulmonary vascular resistance by 2.83±3.1 WU [6]. Based on these studies, it is assumed that the change in mean pulmonary vascular resistance from the start of treatment to 12 months after treatment would be − 4.5 WU for the BPA+R group and − 2.8 WU for the R group, with SD of 2 and 2, respectively. The minimum sample size requires to achieve a significance of 0.05 from a two-sided test with a statistical power of 90%. The combination group is determined to be 54 subjects, and the riociguat group is 27 subjects, for a total of 81 subjects. We estimate the dropout rate to be 15%.

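### The planning SD of 2 WU for the change in PVR is smaller than the figures cited for it allow, so the 90% power claim is not supported as written

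*Protocol article*

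**What the plan says.** The Sample size section of the protocol article prints two sets of source figures. For BPA it reports a study "reducing pulmonary vascular resistance from 7.3±3.2 WU to 3.8±1.0 WU", labelled as mean and SD, within 6 months. For the comparator, "riociguat is reported to decrease pulmonary vascular resistance by 2.83±3.1 WU".

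From these it assumes mean changes at 12 months of minus "4.5 WU for the BPA+R group" and minus "2.8 WU for the R group", "with SD of 2 and 2, respectively". It presents the whole set of assumptions as resting on the two studies. The target is to "achieve a significance of 0.05 from a two-sided test with a statistical power of 90" percent. The result is 54 combination and 27 riociguat patients, 81 in total, with dropout put at 15%.

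The Statistical analysis section sets the primary comparison as an analysis of covariance adjusted for the allocation factors, which the article does not name.

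**The concern.** The planned riociguat mean (2.8) follows the cited mean (2.83) closely, but the SD printed beside that mean (3.1) is replaced by 2 without a reason. For BPA the change SD is not printed, but the two SDs that are printed put a lower limit on it, and 2 lies below that limit. So the plan attributes its variability to sources that contradict it in both arms.

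The change in PVR is the only primary endpoint, and the 90% figure shapes how a non-significant result would be read. If the true SDs are nearer the cited ones, the trial is much less sensitive to a 1.7 WU difference than the article says. Its limitations section mentions small numbers but no shortfall in power.

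**Working it through.** **Inputs.** From Sample size: difference 4.5 − 2.8 = 1.7 WU; SD 2 in each arm; two-sided 0.05; power 90%; 54 + 27; dropout 15%; cited SDs 3.1 (riociguat change) and 3.2 and 1.0 (BPA before and after). From the Abstract and Design: allocation 2:1. Not given: the before/after correlation r in the BPA source, so a range is shown.

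**1. The plan's own figure.** By normal approximation, n(R) = 1.5 × 2² × (1.960 + 1.282)² / 1.7² = 21.8. That is 22 + 44 = 66, or 78 after dividing by 0.85. The t-test version needs 23 + 46 = 69 (power 90.7%), and 69 / 0.85 = 81.2. The stated 81 therefore reproduces, to rounding, as a total that allows for dropout. With all 54 + 27 evaluable, power at SD 2 is 94.5%. The arithmetic is sound; the question is the SD that goes into it.

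**2. What the cited figures imply for the BPA change SD.**
SD(change) = √(3.2² + 1.0² − 2·r·3.2·1.0) = √(11.24 − 6.4r).
- r = 1: √4.84 = 2.20
- r = 0.5: √8.04 = 2.84
- r = 0: √11.24 = 3.35

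An SD of 2 would need r = (11.24 − 4) / 6.4 = 1.13, which is impossible.

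**3. Power at 1.7 WU, unadjusted change.** SE = √(s_B²/n_B + s_R²/n_R), with power from the noncentral t with Welch degrees of freedom. Example for SDs 2.2 and 3.1 at 46 + 23: SE = √(4.84/46 + 9.61/23) = √0.523 = 0.723, and 1.7 / 0.723 = 2.35 on about 33 degrees of freedom, which gives 62.7%. The simpler Φ(2.35 − 1.96) gives 65%.

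| SD combination / riociguat | 46 + 23 (15% dropout) | 54 + 27 (none) |
|---|---|---|
| 2 / 2 (as planned, pooled t) | 90.7% | 94.5% |
| 2 / 3.1 (riociguat corrected only) | 64.0% | 71.4% |
| 2.2 / 3.1 (r = 1) | 62.7% | 70.0% |
| 2.84 / 3.1 (r = 0.5) | 57.7% | 64.9% |
| 3.35 / 3.1 (r = 0) | 53.5% | 60.5% |

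The second row uses only a printed SD and does not depend on r.

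**4. Difference detectable with 90% power at 46 + 23.** The normal approximation is 3.242 × SE: 3.242 × 0.723 = 2.34 WU for 2.2 / 3.1, and 3.242 × 0.814 = 2.64 WU for 3.35 / 3.1. The noncentral t gives 2.4 and 2.7 WU.

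**5. What covariate adjustment would have to deliver.** Bringing an SD s down to a residual of 2 needs a baseline–change correlation of √(1 − (2/s)²): 0.76 for s = 3.1 and 0.42 for s = 2.2.

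**The case against.** Four points can be made for the plan.

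**The analysis is an ANCOVA.** If baseline PVR is a covariate, the printed BPA figures imply a residual SD of at most 1.0 WU in that arm, since 1.0 × √(1 − r²) cannot exceed 1.0. Allowing arm-specific slopes, 46 + 23 would then reach 90% power by normal approximation if the riociguat residual SD were about 2.4, a baseline–change correlation of about 0.63. If that residual stayed at 3.1, power would be about 73%. This stands as a limit on the power figures, which apply to an unadjusted comparison. It does not rescue the paragraph: the article names only unspecified allocation factors, and the sample-size text claims no covariate gain and states no correlation.

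**This population may vary less than the cited cohorts.** Entry requires PVR of at least 4.5 WU. If the cited BPA baseline (7.3 ± 3.2) were normal, about 19% of it would fall below that. Truncation would reduce its SD to about 2.46 and, with the follow-up SD kept at 1.0, the floor for the change SD to about 1.46. So 2.2 is a floor for the cited cohort and not for this trial. That stands too, but the article does not make this argument, and it does not justify 2 in the riociguat arm.

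**The combination mean.** A reader might infer that −4.5 WU is unsupported because BPA alone gave −3.5 (7.3 to 3.8). The documents do not bear that out. The article labels the value an assumption, and it concerns a combination at 12 months, not BPA alone within 6. It lies between −3.5 and the simple sum of about −6.3.

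**The calculation.** A reader might also infer that 81 was miscalculated. It was not; it follows from SD 2.

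**Conclusion.** The sample-size statement is wrong as written. It attributes to two studies an SD that the figures quoted from them rule out: 2 against a printed 3.1 for riociguat, and 2 against a minimum of 2.2 for BPA.

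If the cited variability carries over, an unadjusted comparison at 1.7 WU has about 54–63% power after dropout and about 61–70% without, and the difference detectable with 90% power after dropout is about 2.4–2.7 WU. Correcting the riociguat SD alone already brings power to 64% and 71%.

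These figures assume that the trial's patients vary like the cited cohorts, that the change score is compared without baseline adjustment, and that dropouts leave the analysis. The article instead carries their last value forward, and the effect of that on power is not assessed here. The cited papers themselves were not available.

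A reader might go further and conclude that the trial has little better than an even chance of success, or that 90% power certainly will not be reached. Neither follows. The first fits only the corner with zero correlation and full dropout. The second depends on this trial's SD and on the ANCOVA covariates, which the document does not settle.

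**What to change.** Keep 81 patients and rewrite the paragraph in one of two ways.

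- Replace the SD of 2 in each arm with values that agree with the quoted sources: 3.1 for riociguat, and 2.2 to 3.35 for the combination arm with the assumed before/after correlation stated.
- Or keep 2 and justify it explicitly, for example as the residual SD of an ANCOVA that includes baseline PVR, giving the assumed baseline–change correlation in each arm. The Statistical analysis section should then name baseline PVR as a covariate.

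In either case, give the power at 1.7 WU or the difference detectable with 90% power across the SD range, with and without the 15% dropout, and label each figure as unadjusted or ANCOVA-based.

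This costs a few sentences and no patients. The price is a stated power less favourable than 90%, unless the ANCOVA justification can be made.

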### Eligibility criteria

Inclusion criteria include the following: (a) diagnosis with CTEPH with a WHO functional class II or III based on the diagnostic criteria of the 2015 ESC/ERS guidelines [3]; (b) age ≥ 18 and < 75 years; (c) mean pulmonary arterial pressure of ≥25 mmHg, pulmonary artery wedge pressure of ≤15 mmHg and pulmonary vascular resistance of ≥4.5 WU; (d) administration of appropriate anticoagulant therapy for at least 3 months; (e) provision of written informed consent; (f) patients with non-central CTEPH are not suitable for PEA surgery, or the patient refuses to undergo PEA surgery, or the patient’s general condition is poor and cannot tolerate PEA surgery.

Exclusion criteria include the following: (a) participate in other clinical trials within 3 M before visit 1 or participate in other clinical trials; (b) group 1, 2, 3, 5 pulmonary hypertension; (c) refuse to sign the informed consent form, or unable to cooperate with the investigator during the trial; (d) refuse or unsuitable to BPA; (e) use other targeted medications and other drugs that cannot be combined with riociguat; (f) pregnancy or breastfeeding; (g) contraindicated for riociguat; (h) accompanied by severe chronic or acute liver, kidney or central nervous system diseases; (i) life expectancy of less than 1 years; (j) accompanied by unstable angina, or have a history of myocardial infarction, stroke or life-threatening arrhythmia within 6 months before this test; (k) cannot supine for a long time due to mental factors; (l) patients in the acute infection period; (m) active hemoptysis; (n) obvious obstructive or restrictive lung disease; (o) deemed to be unsuitable for participation by the investigators.

Withdrawal criteria include the following: (a) patient or his legal representative requests to withdraw from the trial; (b) the investigator believes that continuing the experiment will damage the patient's health; (c) in any case, the reason for withdrawal must be recorded in the case report form and the patient's medical record; (d) all patients who withdraw from the trial due to adverse events or abnormal clinical laboratory tests should be followed up until they recover or their condition is stable, and the results should be recorded.

### Recruitment and consent

The informed consent document is presented to potentially eligible subjects to provide a comprehensive explanation of this study. Subjects willing to consider enrollment are consented prior to right-heart catheterization and pulmonary angiography for definitive diagnosis of CTEPH. However, to reduce the burden on the subjects, suitable patients that had undergone comprehensive evaluation, including right-heart catheterization and pulmonary angiography, within 3 months before the consenting can also be enrolled in this study. This is explained to subjects by investigators at the time of obtaining consent. Once consent is obtained, an independent experienced PEA surgeon who is not involved in this study determined operability (whether subjects are eligible for PEA) based on imaging data according to the Guidelines for Treatment of Pulmonary Hypertension [3]. Random assignment is performed centrally and research institutions by biased-coin minimization. In this study, a third-party statistician uses SAS software to perform randomization. The patients are divided randomly through random numbers obtained by the software.

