**Method:**

This study is a single-center randomized controlled trial. Subjects with inoperable CTEPH are randomized into either a BPA combined with riociguat or riociguat monotherapy group (2:1) and observed for 12 months after initiation of treatment. The primary endpoint is the change in pulmonary vascular resistance from baseline to 12 months after initiation of treatment. The secondary endpoints include 6-min walk distance (6MWD), WHO-FC, NT-proBNP, SF-36, and other hemodynamic parameters. Safety endpoints are analyzed too.

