## Methods and analysis

### Design

This study is a singer-center, prospective, randomized controlled trial. As shown in Fig. 1, subjects willing to consider enrollment are consented prior to invasive evaluation. Subjects undergo V/Q scan, right-heart catheterization, and pulmonary angiography for definitive diagnosis of CTEPH by the standard practice based on ESC guideline recommendation [3]. The identified CTEPH patients are provisionally enrolled in this study. An independent experienced PEA surgeon determines if subjects are eligible for PEA. If the subjects are deemed technically operable, they are excluded from this study. All patients who meet the inclusion criteria but don’t meet the exclusion criteria are randomly divided into two groups with 2:1 rate via a randomization application and are observed for 12 months. One group is treated with riociguat only, namely the riociguat group (R group); the other group is given additional BPA therapy on the basis of 3 months riociguat treatment, which is riociguat + BPA group (R+B group). Riociguat tablets are administered orally to all randomized patients at starting dose of 1.0 mg TID and are increased by 0.5 mg increments in 2-week intervals to 1.5, 2.0, and 2.5 mg TID (maximum total daily dose: 7.5 mg) if systolic blood pressure (SBP) is ≥ 95 mmHg and there are no signs or symptoms of hypotension. If higher doses are not tolerated, patients are maintained on lower doses (minimum allowed dose: 0.5 mg TID). After the end of the 8-week titration phase, riociguat is continued at the optimal individual dose for 4 weeks. In the R+B group, patients receive 4 times BPA in 2–3-week intervals in the following 3 months according to the morphology of the pulmonary lesion evaluated by preoperative right-heart catheterization and pulmonary angiography. In general, 3 vessels are performed each time. However, at least among the collaborative institutions included in this study. PEA-inoperable patients are very rarely considered unsuitable for BPA, because the institutes are professional BPA centers in China. Then all participants are followed up to 12 months. And the safety follow-up is up to 30 days later the study completion.

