### Statistical analysis

Data analysis is performed by a specific specialized investigator who keeps being blind to the trial. The research measurement data are presented as mean ± standard deviation, and count data are presented as frequency or percentage. In the baseline characteristics of patients, count data are compared using Pearson’s *χ*^2^ test or Fisher’s exact test and measurement data are compared using *t* test. For primary analysis, the least square means difference and 95% CI for change of pulmonary vessel resistance between groups at 12 months are estimated using analysis of covariance adjusted for allocation factors. For patients who withdraw from the study, the last observation carried forward (LOCF) before withdrawal is used for statistical analysis. Adverse events are evaluated during the safety analysis. The frequencies of adverse events are compared using Fisher’s exact test. We consider the *p* value < 0.05 of two-sided test to be statistically significant. All statistical analysis is performed using SPSS software V22.0. The statistical analysis plan is developed by the principal investigator and biostatistician before the completion of patient recruitment and data fixation.

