### Strengths and limitations of this study

This is a randomized controlled trial comparing the efficacy and safety of BPA combined with riociguat and riociguat alone in patients with inoperable chronic thromboembolic pulmonary hypertension. This study evaluates the efficacy and safety of BPA combined with riociguat over a relatively long period (12 months). This is the first study to compare the efficacy and safety between BPA combined with riociguat and riociguat alone.

The main limitation of this study is the open-label trial design. Because there is no distinct criterion for BPA in each lesion, operators are aware of the mean pulmonary vascular resistance (the primary endpoint in this study), and they might be incentivized to continue BPA. Thus, the bias for the BPA operators cannot be completely avoided. However, since this study compares medical and surgical treatment, it is difficult to use a placebo or mask patients and/or physicians. Other limitations of this study include single-center design and a relatively small number of subjects are recruited.

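### Allocation method and number of centres are not reconciled, so the primary ANCOVA, defined only by its allocation factors, may hold no covariate and does not name baseline PVR

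*Protocol article*

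**What the plan says.** All statements are in the protocol article.

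**Allocation.**
- Design has patients "randomly divided into two groups with 2:1 rate via a randomization application".
- Recruitment and consent says "Random assignment is performed centrally and research institutions by biased-coin minimization".
- The same section continues that "a third-party statistician uses SAS software to perform randomization", and then: "The patients are divided randomly through random numbers obtained by the software".

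**Number of centres.**
- The abstract says "This study is a single-center randomized controlled trial". The first sentence of Design says the same (with a misprint), and Strengths and limitations repeats it: "Other limitations of this study include single-center design".
- Later in Design, a remark on suitability for balloon pulmonary angioplasty (BPA) holds "at least among the collaborative institutions included in this study", and goes on to call the institutes professional BPA centres. The minimisation sentence also speaks of institutions in the plural.

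**Primary analysis.** Under Statistical analysis, the least-squares mean difference in PVR change at 12 months and its 95% CI "are estimated using analysis of covariance adjusted for allocation factors". No other covariate is given for this model.

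**The concern.** Biased-coin minimisation assigns each patient from the running balance on named factors. Division by random numbers, read plainly, needs no factors. The article does not say how the two statements fit together, or how the randomisation application relates to either. The minimisation sentence is also garbled at the point where a factor might have been named.

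In many protocols this would be a drafting matter. Here it reaches the primary endpoint, because the covariates of the primary model are defined by reference to the allocation scheme. If the scheme cannot be determined, neither can the model. The only factor the text hints at is institution, which is constant in a one-centre trial. For a change-from-baseline endpoint the natural covariate is the baseline value, and the stated model includes it only if baseline PVR happens to have been an allocation factor.

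**Working it through.** **1. The plan's own figure.** Inputs from Sample size: mean changes −4.5 and −2.8 WU (difference 1.7), SD 2 in each arm, two-sided 0.05, power 90%, dropout 15%; the 2:1 ratio is from Design.

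- Normal approximation, smaller arm: 1.5 × [2 × (1.960 + 1.282) / 1.7]² = 21.8, so 22 + 44 = 66.
- t test (noncentral t): 23 + 46 = 69, power 90.7%.
- Dropout: 69 / 0.85 = 81.2, against the stated 81 (54 + 27).

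The total is thus reproduced to rounding. It comes from an unadjusted comparison of two means, so it does not depend on the allocation method, the number of centres or the covariates.

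**2. What the stated ANCOVA contains under each reading.**

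| Reading of the text | Allocation factors | Primary model for PVR change |
|---|---|---|
| One centre, minimisation on institution | Institution, one level | Constant column, absorbed by the intercept: arm only |
| One centre, random numbers without factors | None | Arm only |
| Several centres, minimisation on institution | Institution | Arm + centre |
| Minimisation or a stratified list on factors given only in a fuller document | Those factors | Arm + those factors; baseline PVR only if it is one of them, possibly only as a class |

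Under the first two readings the ANCOVA reduces to a two-sample comparison of mean change. The third contains no baseline PVR, and the fourth cannot be checked from this article.

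**3. Is baseline PVR available?** Yes. Table 1 schedules right-heart catheterisation at Visit 1 and Visit 4, and eligibility requires a PVR of at least 4.5 WU, so every randomised patient should have a value.

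**4. What adjusting for it would be worth.** With a linear covariate, the residual SD is SD × √(1 − ρ²), where ρ is the within-arm correlation between baseline PVR and change in PVR. The document gives no ρ; 0.3 to 0.7 in absolute size is my assumption. Unadjusted standard error at 46 and 23 evaluable: 2 × √(1/46 + 1/23) = 0.511 WU.

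| Assumed ρ (absolute) | √(1 − ρ²) | Standard error (WU) | Reduction |
|---|---|---|---|
| 0.3 | 0.954 | 0.487 | 5% |
| 0.5 | 0.866 | 0.442 | 13% |
| 0.7 | 0.714 | 0.365 | 29% |

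The cost is one degree of freedom out of 67 (69 − 2), which is negligible.

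**The case against.** **The allocation sentences may describe one procedure.** Biased-coin minimisation itself uses random numbers, and a third-party statistician can run it in SAS and deliver it through an application. This stands: the descriptions are unreconciled, not incompatible. SAS random numbers can also generate a stratified list, so a reader should not infer that factors exist only under minimisation.

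**The factors may be listed elsewhere.** A journal article condenses the protocol, and settling covariates in an SAP is ordinary. The article says the SAP is written by the principal investigator and biostatistician before recruitment is complete and data are fixed, and that the analyst is blinded. This also stands, so the missing list is not the finding, and the text does not support an inference that covariates will be picked after seeing results. A fuller document does not, however, remove the conflict over the number of centres, or change a stated primary model that leaves out baseline PVR.

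**Stronger readings that do not hold.**
- *Power is lost through an uneven split.* This presumes simple randomisation, which the document never states. Even then, averaging power over a Binomial(81, 1/3) riociguat arm with 15% loss gives 90.0%, the plan's target.
- *Chance imbalance in baseline PVR biases the result.* Under randomisation, chance imbalance is already counted in the standard error and the type I error. Nor can its effect be made very large on the plan's inputs: with an SD of change of 2 and the cited baseline SD of 3.2 WU, the slope of change on baseline cannot exceed 2 / 3.2 = 0.625 in size.
- *Centre and operator effects go unadjusted.* If several institutions enrol and institution is the minimisation factor, the stated ANCOVA does adjust for centre. The article also says that two specific surgeons perform all BPA.

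**Conclusion.** The point holds in a limited form. The article contradicts itself on the number of centres and leaves three descriptions of allocation unreconciled. Because the primary ANCOVA is defined only through allocation factors, its covariates cannot be determined from the text. Under the single-centre statement, which the article makes three times, the only factor hinted at vanishes and the model may have no covariate.

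The effect is on clarity and efficiency, not validity. The unadjusted comparison is unbiased under randomisation, the total of 81 stands, and no loss of power against the plan's target is shown. Naming baseline PVR is an improvement at no cost. Its size, a standard error about 5% to 29% smaller, rests on the assumed correlation of 0.3 to 0.7, a linear relation and the plan's SD of 2. Whether the true allocation factors already include baseline PVR cannot be known from this document.

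**What to change.** - **Statistical analysis:** state that the primary ANCOVA adjusts for baseline PVR as a continuous covariate plus every factor actually used in allocation. The allocation factors should be kept, not replaced.
- **Design, and Recruitment and consent:** describe the one allocation method actually used, how the central system, SAS and the application fit together, and the factors, if any.
- **Number of centres:** state it once. If there is one, delete the references to collaborating and research institutions. If other sites enrol, correct the single-centre statements and include centre in the model.

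The method should be reported as it was run. No new minimisation factors are needed, and a randomisation in progress should not be altered. The cost is a wording amendment and one covariate that is already collected; no extra patients, visits or measurements are required.
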